### Data collected by the PEGASO system

The interaction between the user and the Pegaso system is recognized through of a set of automatic engagement indicators measuring the actual usage of the system. For each participant, actions like interacting with the Companion app or registering a meal in the EDiary app are tracked and daily stored. The EDiary app records information about the reported meals composition, food groups and servings. The smartphone collects information about physical activity such as the number of steps or the total time spent doing physical activity. Further information on physical activity is collected from the 4th month by the introduction of a smart bracelet and smart sensor. General information about healthy habits is gathered through the “Self-Report Habit Index (SRHI)” adapted to include items that reflect self-identity [44]. The questionnaire appears as a notification inside the Companion app in between the achievement of a target behaviour and the selection of a new one. Self-awareness is recorded by the PEGASO system using the COM-B-Q Self-Assessment Questionnaire (Capability, Opportunity and Motivation for Behaviour) [45]. It is a questionnaire, based on the principles of behaviour change, about current behaviours and insight into aspects that need to be acted upon in order to achieve a pre-specified behavioural goal. The questionnaire appears as a notification inside the Companion app just after the selection of a new target behaviour.

### Analysis plan and statistical analysis

The analysis plan will include a description of all data at every assessment point and an overall comparison of baseline characteristics between intervention group (IG) and comparison group (CG), as well as by sites and gender. Knowledge/awareness, lifestyles and anthropometric measurements will be compared at pre and post intervention (month 6) utilising an intention-to-treat (ITT) approach, independently from drop-outs and non-adherence. Relevant changes among lifestyles and knowledge will be defined according to current recommendations from international guidelines [46]. The effect of the intervention could be modified by gender, cultural and socioeconomic level, body mass index (BMI), as well as by the baseline lifestyles, which will be controlled in the analysis. Changes in motivation will be assessed in the four assessment points and compared to baseline. For the intervention group, the results from SUS, EMO, satisfaction, trust and reputation questionnaires will be compared from month 4 to month 6. The level of engagement in the PEGASO platform will be assessed from indicators of usage at individual level, such as the number of days of interactions with the APPs or the daily number of steps, stored in the cloud.

Results will be reported as mean ± standard deviation (or median, percentile 25 and 75) for quantitative variables or frequency and percentage distribution for qualitative variables. Quantitative variables will be tested for normality, log-transformed if needed, and accordingly analysed with parametric or non-parametric methods. Chi-squared test will be used to analyse the association between independent qualitative variables, along with the McNemar test for paired samples. The Student t-test will be used for the comparison of means between two groups, and the paired t-test will be applied to assess changes within one same group. Alternatively, the corresponding nonparametric tests will be used, as required. The relationship between quantitative variables will be analysed using Pearson’s correlation coefficient or Spearman coefficient in the case of asymmetrically distributed variables. Techniques of principal component analysis (PCA) will be applied to identify patterns of variables best explaining outcomes of interest.

Multivariate linear regression analysis and logistic regression analysis will be used to analyse the variables determining the changes in physical activity and eating and sleeping habits. In order to analyse the effect of the intervention, comparison will be made of the changes observed in the CG versus the IG, with estimation of the Cohen d statistic, adjusting for the variables that may influence the results.

The level of statistical significance will be set at α = 0.05 and all tests will be two-tailed. Statistical analyses will be carried out using the software packages SPSS, version 22.0 (SPSS Inc., Chicago, IL) and Stata (StataCorp. 2009. Stata Statistical Software: Release 11. College Station, TX: StataCorp LP). Focus groups will analysis will be done with the support of Atlas. Ti /NVIVO and by triangulation of analyst.

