### Recruitment and group allocation

Potential participants were identified in schools, which were approached through researcher’s contacts. The selection of schools was determined by our aim to include students from a range of socioeconomic backgrounds. Different recruitment strategies were applied in the schools. In two sites, whole classes were recruited to the intervention group and whole classes to the control group (from the same school or from a different one). Another recruitment strategy was that the intervention was offered to all students in eligible year groups and volunteers were sought with the first responders being chosen. Participants for the control group were similarly chosen from another school. Participant recruitment took place from September to November 2016.

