### Outcomes and variables

The first block of outcomes that will be assessed are related to recruitment and adherence to the intervention, namely recruitment rate, study retention, adherence to the intervention and attitudes to the different components of the intervention.

We aim to test a range of outcomes related to individual lifestyle (dietary habits, physical activity, sedentary behaviour, and sleeping habits), knowledge/awareness about these health habits and user experience of the platform. Individual lifestyle and knowledge/awareness about health habits are assessed at baseline and at the end (6 months) of the intervention both in the comparison and intervention group. User experience is assessed at month 2, 4 and 6 only in the intervention group. Outcomes, instruments and assessment points during the study are detailed in Table 3.

**Table 3 Tab3:** Outcomes, instruments and assessment points in the PEGASO study

Outcome	Instrument	Assessment point			
		BL	M2	M4	M6
Dietary habits	Mediterranean Diet Quality Index in children and adolescents (KIDMED questionnaire) + 5 additional questions	X			X
Physical activity	Physical Activity Questionnaire for Adolescents (PAQ-A) + 3 additional questionnaires	X			X
Sedentary behaviour	Screen time-based sedentary behavior questionnaire (SSBQ)	X			X
Sleeping habits	Sleep Habits Survey (SHS)	X			X
Knowledge questionnaire	Ad hoc questionnaire	X			X
Anthropometric Measurements		X			X
Height	Stadiometer SECA 213	X			X
WC	Flexible graduated measuring tape (SECA 201)	X			X
Weight	*England, Catalonia, Italy*: Homologated	X			X
BMI	electronic scale Tanita SC240MA				
% of body fat	*Scotland*: Tanita MC780MA Multi	X			X
% of body water	Frequency Segmental Body Composition Analyser	X			X
Family affluence and self-reported health status	Family Affluence Scale (FAS) + 1 question from the Social Functioning subscale −12 (SF-12)	X			
*Motivation*	*Perceived Competence Scale*	*X*	*X*	*X*	*X*
*Usability*	*System Usability Scale*			*X*	*X*
*Emotional Response to the Platform*	*Emotional Metric Outcome questionnaire*			*X*	*X*
*Satisfaction, Trust, Reputation*	Ad hoc *questionnaire*			*X*	*X*
*User Experience*	*Focus Groups*			*X*	*X*

In italics, outcomes assessd only in the intervention group. All the other outcomes were assessed in both, intervention and comparative group

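### Baseline knowledge is scored in both arms but is not a committed covariate for the knowledge comparison, which costs precision and leaves the handling of a baseline gap between non-random arms open

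*Protocol article*

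**What the plan says.** In the Protocol article, the Outcomes and variables section states: "Individual lifestyle and knowledge/awareness about health habits are assessed at baseline and at the end (6 months) of the intervention both in the comparison and" the intervention group. Table 3 confirms a knowledge questionnaire at baseline and month 6, and does not mark it as restricted to the intervention group.

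The Analysis plan and statistical analysis section names possible effect modifiers and says they will be controlled: gender, cultural and "socioeconomic level, body mass index (BMI), as well as by the baseline lifestyles, which will be controlled in the analysis". The same section keeps knowledge apart from lifestyles: "Knowledge/awareness, lifestyles and anthropometric measurements will be compared at pre and post intervention (month 6"). Outcomes and variables does so too, giving lifestyle as diet, physical activity, sedentary behaviour and sleep. The term for baseline lifestyles therefore does not naturally cover the knowledge score.

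The effect is defined as follows: "comparison will be made of the changes observed in the CG versus the IG, with estimation of the Cohen d statistic", with the addition "adjusting for the variables that may influence the results". That addition names no variables. The regression sentence just before it covers physical activity, eating and sleeping habits, and does not mention knowledge.

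Allocation was not random. In two sites whole classes were taken. Elsewhere "volunteers were sought with the first responders being chosen", and the comparison group was chosen similarly from another school.

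**The concern.** Knowledge is the first effect in the study's list of aims, and the Discussion counts it among the main results. The plan commits to controlling baseline status for lifestyles and BMI, but makes no such commitment for knowledge, although the baseline score is already collected.

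Subtracting the baseline is not the same as adjusting for it. A change score fixes the slope on baseline at 1. Adjustment estimates that slope, which for a repeated quiz score is usually below 1. Two things are at stake:

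- **Precision.** The change contrast is noisier than it need be. Design and settings says the study should indicate outcome variance for sizing a future cluster randomised trial. If the knowledge variance carried forward were that of the change score, the size of that trial would be inflated by the same factor.
- **Interpretation.** Classes, volunteers and schools can differ in baseline knowledge. The estimate then depends on how that gap is handled, and the article leaves this open for knowledge.

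**Working it through.** **Inputs from the article.** Target 525 at 2:1, so 525 × 2/3 = 350 intervention and 525/3 = 175 comparison; two-sided α = 0.05. The article gives no SD, effect size, power or dropout rate, so there is no power figure to reproduce.

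**Assumptions.** Equal SD of 1 at both times; baseline-to-month-6 correlation ρ of 0.3 to 0.9; a common within-arm slope equal to ρ; an illustrative effect of 0.25 SD; baseline gap d₀ (intervention minus comparison) of 0.2 or 0.5 SD. Other covariates, clustering and dropout are ignored.

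**Precision.** Var(change) = 2(1−ρ). Var(adjusted) = 1−ρ². Their ratio is 2(1−ρ)/[(1−ρ)(1+ρ)] = 2/(1+ρ).

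SE = √[Var × (1/350 + 1/175)], where 1/350 + 1/175 = 0.00857. The difference detectable with 80% power is (1.960 + 0.842) × SE. At ρ = 0.5 the change score has SE = √(1.00 × 0.00857) = 0.0926, so the detectable difference is 2.802 × 0.0926 = 0.259 SD.

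| ρ | Var change | Var adjusted | Ratio | Detectable SD, change / adjusted | Power at 0.25 SD, change / adjusted |
|---|---|---|---|---|---|
| 0.3 | 1.40 | 0.91 | 1.54 | 0.307 / 0.247 | 62.6% / 80.8% |
| 0.5 | 1.00 | 0.75 | 1.33 | 0.259 / 0.225 | 77.0% / 87.7% |
| 0.7 | 0.60 | 0.51 | 1.18 | 0.201 / 0.185 | 93.7% / 96.6% |
| 0.9 | 0.20 | 0.19 | 1.05 | 0.116 / 0.113 | about 100% / about 100% |

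**Cost of adjusting when a gap exists.** The adjusted variance is inflated by 1 + p(1−p)d₀² with p = 2/3. For d₀ = 0.5 this is 1 + (2/9)(0.25) = 1.056, and the ratios fall to 1.46, 1.26, 1.12 and 1.00. At ρ = 0.9 with that gap the gain is gone.

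**Effect of a baseline gap.** Let τ be the true effect.

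- *Arms comparable given baseline.* The expected month-6 difference is τ + ρd₀. The change contrast is τ + ρd₀ − d₀ = τ − (1−ρ)d₀, so it is off by −(1−ρ)d₀. The adjusted contrast gives τ.
- *Gap stable over time (parallel trends).* The expected month-6 difference is τ + d₀. The change contrast gives τ. The adjusted contrast is τ + d₀ − ρd₀, so it is off by +(1−ρ)d₀.

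| ρ | Size of bias, d₀ = 0.2 SD | Size of bias, d₀ = 0.5 SD |
|---|---|---|
| 0.3 | 0.14 | 0.35 |
| 0.5 | 0.10 | 0.25 |
| 0.7 | 0.06 | 0.15 |
| 0.9 | 0.02 | 0.05 |

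The size is the same in both cases; only the sign and the estimator affected change.

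**Compatibility with the plan.** Regressing the change on arm and baseline gives the same arm coefficient as regressing the month-6 score on arm and baseline. The plan's adjusted comparison of changes can therefore stay; it needs only the baseline score as a named covariate.

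**The case against.** The strongest reply is that the list is not closed. It names possible effect modifiers, and the later clause allows adjustment for any variable that may influence the results. Baseline knowledge fits that clause, and covariate lists per outcome are often left to a fuller document. This stands to the extent that a reader might infer that the plan excludes baseline knowledge, and the text does not say so. But the article does choose to name the baseline variables it controls, and an open clause lets the covariate be chosen after the data are seen.

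Second, comparing changes is a recognised method for non-equivalent groups and is valid under parallel trends. This stands. A reader might infer that the change score carries the baseline imbalance into the result, or that adjustment is the unbiased choice. Neither follows: subtraction removes the raw gap, and what can remain is regression to the mean, opposite in sign to the gap. Adjustment has its own bias if the gap is stable. Measurement error in a quiz that is partly ad hoc adds to the doubt.

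Third, every size rests on assumed values, and the benchmark is a change score without the covariates the plan already promises. Any association of those with baseline knowledge would shrink the gain. This also stands.

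Finally, knowledge is not the only outcome affected: waist circumference and body composition are measured in both arms, and their baselines are not named either.

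**Conclusion.** The point holds in a limited form. Baseline knowledge is measured in both arms, falls outside the named control list, and is not secured by the open clause. Leaving it out costs precision: 54%, 33% and 18% extra variance at assumed ρ of 0.3, 0.5 and 0.7, with little or no cost near 0.9. These figures precede other covariates, clustering and dropout. Clustering would lower all the power figures.

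On bias, the documents do not settle which estimator is right. For a 0.2 SD gap at ρ = 0.5, either can be off by 0.10 SD, in opposite directions, depending on which assumption is true. That is a reason to prespecify both, not to demote the change contrast to description.

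A reader might also infer that the trial is underpowered for knowledge. The article does not support that: 525 is justified by recruitment, socioeconomic spread, attrition and variance estimation, so no stated power is lost and no stated figure is wrong. This is a cheap improvement that should be made, not the correction of an error in a number.

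**What to change.** In Analysis plan and statistical analysis, extend the item on baseline lifestyles to: *the baseline value of the outcome analysed, including the baseline knowledge score*. This wording also covers waist circumference and body composition.

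Estimate the knowledge effect and its adjusted Cohen d from a regression that includes arm, baseline knowledge and the covariates already listed. Report the change-score contrast beside it as a prespecified sensitivity analysis, and say that the two rest on different assumptions about any baseline gap.

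The cost is a sentence or two and no new data. The downside is that the two results can differ in non-random arms and the reader will have to weigh them. Measurement error in the quiz will also leave some residual imbalance after adjustment.

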Self-monitoring of behaviour Feedback on behaviour	Display of stats about user behaviours
Social support	Provision of the possibility to interact with the family doctor

*UI*: User interaction

The innovative key component of the PEGASO system is the behaviour recognition system, which allows detection and evaluation of participants’ real-time behaviour (collected through other components of the PEGASO system). A summary of the obesity-related behaviours targeted by the PEGASO system is shown in Table 2.

**Table 2 Tab2:** Target behaviours of the PEGASO system and behavioural goals

Target behaviour	Behavioural goals
Dietary target behaviours	- Fruit consumption of ≥2 servings (250-375 g)/day
	- Vegetable consumption of ≥2 servings (300-450 g)/day
	- Reduced intake of sugar-sweetened beverages
	- Daily breakfast consumption
	- Reduced intake of fast food
	- Reduced consumption of sweet and salty high-energy snack high-energy
Physical activity target behaviours	- 60 min of daily physical activity of moderate-to-vigorous intensity (i.e. involving energy expenditure over 4 METs)
	- Undertake 12.000 steps/day
	- Daily active transport to and from school
Sedentary behaviour	- less than 45% of after-school time daily spent in sedentary activities (≤1.5 METs)
Sleep behaviour	-Daily sleep duration of at least 8 h

*METs* Metabolic Equivalents

Participants have the opportunity to choose one target behaviour at the time. When selecting a new target behaviour, participants are asked to complete the COM-B questionnaire [30]. The answers for each question subset guide which component of the COM-B behaviour system is adopted to target the content of the behaviour change intervention. For instance, the messaging framework in the PEGASO Companion App selects messages that are associated with participants’ preferences expressed in the COM-B questionnaire. This provides an intervention that is personalised to the different needs of the individual intervention participant.

The PEGASO system was developed using a user-centred design approach aiming to deliver a product and interactions which are attractive to adolescents and which enabled them to connect with their peers.

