### Procedures

Eligible participants are introduced to the PEGASO system after they and their parents/guardian provided written and signed consent, and after baseline measurements are collected. Participants are provided with a smart phone (running as OS Android, version from 4.4 to 6.0) with the PEGASO apps installed for the duration of the study.

Given the complexity of the PEGASO system, the components are introduced in two sessions within the same first week. The physical activity monitors are introduced to the participants at the mid-point assessment time at month 4 of the study. This time point was chosen to reduce the burden on the schools and participants, allocating time and resources in addition to the baseline measures, mid-point and follow-up assessment contact points, whilst additionally avoiding conflict with exam timetables and extended holiday periods (e.g. summer break). In addition to familiarising the participants with the functionalities and use of the garment and activity monitors, researchers assist participants in connecting the activity monitors with individual smart phones. All introduction sessions across the four study sites provide a mixture of interactive workshops, educational games, and replicate the method as much as possible within the constraints of the school requirements in different countries.

Participants are offered support during the study to facilitate understanding of how to use the PEGASO system and to trouble-shoot any issues arising. Participants are invited to join a site specific Google Hangout group to allow timely communication with the field researchers who provide solutions to technical issues whenever possible. Teachers at schools are offered a brief training session to be able to answer simple questions related to the use of the PEGASO system. They are asked to direct the participants to the web portal and the FAQ link for questions they cannot answer.

The role of teachers is to support students over the testing period, and to facilitate the communication flow among field researchers, parents and teenagers. During on-site contact points an interaction with teachers is expected; they will have the opportunity to indicate to the field researchers any comments, doubts or conflicts including maladaptive behaviours.

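### The daily step count is listed as an indicator of platform use, although the protocol treats steps as a target behaviour, so an engagement measure that contains it partly measures physical activity.

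*Protocol article*

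**What the plan says.** Under Analysis plan and statistical analysis, the protocol article states: "The level of engagement in the PEGASO platform will be assessed from indicators of usage at individual level". It gives two examples: "such as the number of days of interactions with the APPs or the daily number of steps, stored in the cloud". Daily steps are thus one of only two indicators named.

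Under Data collected by the PEGASO system, the article describes a "set of automatic engagement indicators measuring the actual usage of the system". Its examples there are interacting with the Companion app and registering a meal. The same section then covers steps under a different purpose: "The smartphone collects information about physical activity such as the number of steps or the total time spent doing physical activity".

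Table 2, in the Intervention section, lists "Undertake 12.000 steps/day" among the physical activity goals that the system tries to bring about.

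On timing, Procedures says "The physical activity monitors are introduced to the participants at the mid-point assessment time at month 4 of the study", and the section on system data adds: "Further information on physical activity is collected from the 4th month by the introduction of a smart bracelet and smart sensor".

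**The concern.** Engagement should record whether a participant used the system. A step count records how much the participant walked while a device was counting. A pupil who carries the study phone, walks a great deal and seldom opens an app would look engaged on this indicator. A pupil who uses the apps heavily and is sedentary would look disengaged.

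This matters in a study centred on feasibility and acceptance:

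- Adherence to the intervention is in the first block of outcomes (Outcomes and variables), and engagement is listed there as a factor of user experience.
- The Discussion gives as a purpose the understanding of how user experience relates to health behaviours and habit formation. If the exposure contains steps and the outcome is physical activity, part of any association is activity with activity.
- Focus groups are to mix participants with different levels of engagement where possible. A level based on steps could separate active from inactive pupils rather than users from non-users.

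There is a smaller issue of timing. New sensors arrive at month 4 and the article does not say which device supplies the step count afterwards. A shift in recorded steps at that point could come from measurement and be read as a change in engagement.

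**Working it through.** The plan gives no figure to reproduce. The point concerns how a variable is defined, so the check is to set the relevant statements side by side.

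| Place in the protocol article | Treatment of steps or engagement |
|---|---|
| Analysis plan and statistical analysis | Daily steps are an example of a usage indicator for engagement |
| Data collected by the PEGASO system | Engagement indicators measure actual use; examples are app interaction and meal registration |
| Data collected by the PEGASO system | Phone steps are physical activity information |
| Intervention, Table 2 | 12.000 steps/day is a physical activity goal |
| Outcomes and variables, Table 3 | The physical activity outcome is the PAQ-A questionnaire with additional questions, at baseline and month 6 |

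**Step 1: consistency.** The first row conflicts with the next three. Three statements place steps on the behaviour side, or define engagement in a way that leaves them out. One places them on the usage side.

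**Step 2: consequence for an association.** Let U be app use, S the step count and A the measure of physical activity. For an engagement measure E = aU + bS, with a and b not negative,

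cov(E, A) = a·cov(U, A) + b·cov(S, A).

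The second term is positive whenever b > 0 and steps are positively related to A. This holds even if app use is unrelated to activity, that is, cov(U, A) = 0. There are two limiting cases:

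- b = 0 (app-interaction days only): the second term vanishes and the problem does not arise.
- a = 0 (steps analysed as an indicator on their own): the whole association is between two measures of activity.

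The documents give neither weights nor a correlation between steps and PAQ-A, so the direction can be argued but the size cannot be computed.

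**Step 3: reach.** The system is given to the intervention group only, so the engagement indicators exist only there. The effect analysis compares changes between the two groups and does not use them. That comparison is unaffected.

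**Step 4: month 4.** The phone collects steps. From month 4 a bracelet and a smart sensor supply further activity information. According to Physical activity monitors, their data pass to the phone and are linked to the Companion app, the Dashboard app and the game. The Dashboard shows steps. No section says whether the step count then stays phone-based, is merged with bracelet data or is replaced by it. A measurement shift is possible but not established.

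**The case against.** The strongest reply is that this is one badly chosen example. The section on system data already defines engagement correctly, and the exact list of indicators could be left to a fuller document. The article says indicators in the plural, introduced as examples, and plans no composite score. It specifies no regression of activity on engagement: the planned regressions concern determinants of lifestyle change and do not list their predictors. The link between user experience and behaviour is stated as a purpose in the Discussion, where user experience is a broad construct with many factors. Recorded steps also carry some usage information, because the study phone must be carried for them to be counted.

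Most of this stands, and it limits the point. It does not remove it, because the article does more than stay silent: it names steps as a usage indicator. What steps reveal about carrying a device is captured by whether any data arrived that day. The count adds behaviour.

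A reader might infer three stronger claims that the documents do not support:

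- That every link between engagement and activity is circular. App-interaction days related to PAQ-A would not be. Even with steps included, the overlap is between related constructs, since the outcome is a questionnaire and not the step count.
- That the source of step data switches at month 4. The text says information is added.
- That a particular inflated correlation or p-value will result. Any such figure needs an assumed index, assumed weights and an assumed correlation, none of which is in the article. The planned regressions also concern changes in behaviour, and a correlation between steps and activity level need not carry over to change.

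**Conclusion.** The point holds as a mis-specified measure. The analysis plan classes as usage something that the rest of the article classes as behaviour, and an engagement measure that includes it would be biased towards a positive association with physical activity. This rests on two assumptions: that the indicator is used as written, and that steps and the activity measure are positively related. The size is not determinable from the documents.

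The consequence is confined to intervention-group descriptions of engagement and to analyses relating engagement to activity. Conclusions about the effect of the intervention against the comparison group do not depend on it. The month-4 matter is a gap in the description of the step source, to be handled in reporting. It is not evidence of an artefact. The change is worth making because it is nearly free and protects a measure close to the study's main purpose.

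**What to change.** In Analysis plan and statistical analysis:

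1. Remove the daily step count from the engagement indicators and report it as a behaviour measure in the intervention group.
2. Define engagement from tracked use: days with app interaction, meals registered in the EDiary, and days on which any phone or bracelet data were received, regardless of the count. Tabulate the data-received days by device, since bracelet days cannot occur before month 4.
3. State which device supplies the step count before and after month 4. Report phone-derived steps across all 6 months and bracelet data separately from month 4.

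The cost is two or three sentences. App interactions and meal registrations are already tracked and stored daily. Days with device data should be derivable from the stored activity records, which the data managers should confirm. No new data collection is needed and no planned comparison between groups changes.

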## Methods

### Design and settings

A quasi-experimental cluster controlled trial was undertaken to evaluate an ICT-based intervention over 6 months, i.e., the PEGASO System, to promote healthy habits among adolescents. This study includes adolescents of 12 schools from four sites: England (UK), Scotland (UK), Lombardy (Italy) and Catalonia (Spain).

The target sample size of 525 with 2:1 allocation (intervention: control) was designed to be large enough in each school to be reasonably sure that large scale recruitment was possible, to have a representation from different socioeconomic groups, to allow for attrition and to give some indication of variance in the various proposed outcome measures which would permit a sample size calculation for a future cluster randomized controlled trial.

Ethical approval was granted by the clinical research ethics committee (CEIC) of all four intervention sites: South East Scotland Research Ethics Committee in the UK, Istituto di Ricovero e Cura a Carattere Scientifico (IRCCS) Policlinico of Milan in Italy and CEIC of Institut d’Investigació en Atenció Primaria de Salut Jordi Gol (IDIAP Jordi Gol) in Spain.

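### The arm is set by class or by school, but the named between-group tests treat pupils as independent, so for any positive intracluster correlation the type I error exceeds 5%

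*Protocol article*

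**What the plan says.** Design and settings gives the design: "A quasi-experimental cluster controlled trial was undertaken to evaluate an ICT-based intervention over 6 months". It also gives the number of schools: "This study includes adolescents of 12 schools from four sites". The target is 525 pupils at 2:1, that is 350 intervention and 175 control. One of the reasons given for that size is to obtain variance information "which would permit a sample size calculation for a future cluster randomized controlled trial".

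Recruitment and group allocation describes two routes. In two sites "whole classes were recruited to the intervention group and whole classes to the control group", and the two sets of classes could come from one school or from different schools. Under the other route, early volunteers from eligible year groups formed the intervention group, and the controls were drawn in a similar way from another school.

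Analysis plan and statistical analysis names the methods. For means, "The Student t-test will be used for the comparison of means between two groups". Chi-squared is named for categorical variables, with nonparametric alternatives where needed. "Multivariate linear regression analysis and logistic regression analysis will be used to analyse the variables determining the changes" in activity, eating and sleep. The intervention effect is the difference in change between arms, expressed as an adjusted Cohen d. All tests are two-sided at 0.05. The characteristics listed for control are gender, cultural and socioeconomic level, BMI and baseline lifestyle. Neither school nor class is among them. No random effect, GEE, cluster-robust standard error, cluster-level summary or ICC is mentioned.

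**The concern.** Pupils in the same class or school share teachers, timetable, canteen, neighbourhood and peers, so their outcomes are likely to be correlated. When the arm is also fixed at class or school level, chance differences between classes or schools go straight into the arm contrast. A pupil-level t-test, chi-squared test or ordinary regression counts each pupil as a separate piece of evidence and leaves that component out of the standard error.

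At stake are the p-values and intervals for diet, activity, sedentary time, sleep, knowledge and anthropometry: ordinary differences between schools could be reported as effects of PEGASO. A secondary consequence concerns planning. A pupil-level SD on its own cannot size a cluster trial, because that calculation also needs the ICC.

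The article goes beyond leaving detail to a fuller plan: it names specific tests, a significance level and software, and the named tests do not match the named design.

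**Working it through.** **Reproducing the plan's figure.** 525 cannot be reproduced. The article gives no effect size, SD, power, ICC or dropout rate, and does not present 525 as a power calculation.

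**Inputs from the article.** N = 525, split 350:175; 12 schools; two-sided alpha 0.05.

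**Assumed inputs.** ICC 0.01, 0.05 and 0.10; equal cluster sizes; a class-sized cluster of 22. The article gives none of these.

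**Formulas.** Design effect DE = 1 + (m − 1) × ICC, where m is the number of pupils per cluster. True SE = naive SE × √DE. True error of the nominal 5% test = 2 × [1 − Φ(1.96/√DE)].

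**Case A: every school in one arm.** m = 525/12 = 43.75.

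| ICC | DE | naive SE as % of true SE (100/√DE) | 1.96/√DE | true error |
|---|---|---|---|---|
| 0.01 | 1 + 42.75 × 0.01 = 1.43 | 84 | 1.64 | 10% |
| 0.05 | 1 + 42.75 × 0.05 = 3.14 | 56 | 1.11 | 27% |
| 0.10 | 1 + 42.75 × 0.10 = 5.28 | 44 | 0.85 | 39% |

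A simulation of 8 against 4 schools of 44 pupils (10,000 runs per ICC) agrees. The pupil-level t-test rejected in 10.2%, 26.4% and 40.1% of null data sets. A t-test on school means stayed between 4.9% and 5.1%.

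**Case B: class-sized clusters, m = 22 (assumed).** DE = 1 + 21 × ICC = 1.21, 2.05 and 3.10. The true error is 7.5%, 17% and 27%.

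**Case C: some schools hold both arms.** The article allows this but does not say how many schools are involved. Where both arms share a school, the school effect partly cancels. Simulations of 12 schools of 44 pupils, with school-level ICC only, gave:
- 3 shared schools: roughly 8.5 to 9%, 21 to 22% and 34%;
- 6 shared schools: about 8%, 17% and 27%.

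**Effect on the interval.** Naive SE = √(1/350 + 1/175) = 0.0926 SD, so the 95% half-width is 1.96 × 0.0926 = 0.18 SD. In Case A at ICC 0.05 the SE is 0.0926 × √3.1375 = 0.164 SD and the half-width is 1.96 × 0.164 = 0.32 SD. With site as a fixed effect and allocation by school, 12 − 4 − 1 = 7 degrees of freedom remain (t = 2.365), and the half-width is 2.365 × 0.164 = 0.39 SD.

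**Precision of an ICC from this study.** By the exact F method with 10 between-school degrees of freedom, an observed ICC of 0.05 has a 95% interval of about 0.013 to 0.17.

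**The case against.** The strongest reply is that this is mainly a feasibility study. The size is not power-based, recruitment and adherence come first among the outcomes, and the Discussion says that the aim is to test the methodology. It also calls PEGASO an individual rather than a school-based intervention. This bears on how much weight the tests carry, but does not remove the mismatch: the Abstract lists effectiveness as an aim, the analysis section plans between-group comparisons at two-sided 0.05, and correlation comes from shared classes and schools however the intervention is delivered.

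The size of the inflation is also open to challenge, and this stands. Every ICC is assumed. The planned contrast is change, with adjustment for baseline lifestyle and socioeconomic level, and clustering may be weaker there than in raw scores. The school-level figures need every school to sit in one arm, which both the recruitment section and the Discussion leave open. A reader might infer that whole schools were allocated, or that error rates of 27% to 39% are to be expected. The article supports neither: it describes whole classes or volunteers within schools, so those figures are an upper case under assumed ICCs.

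Adjustment for variables that may influence the results could be stretched to include site. A site covariate does not replace a school or class term.

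Finally, the fuller plan may provide for an ICC. That is fair, and it makes the ICC a secondary point.

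**Conclusion.** The point holds: the named between-group analysis does not fit the stated design. For any positive ICC in the units that set the arm, the standard errors are too small and the type I error exceeds 5%. The direction follows from the allocation described. The size depends on assumptions: for ICC 0.01 to 0.10 it runs from about 7.5% to 27% with class-sized clusters, and from about 10% to 39% if no school holds both arms. Mixed layouts fall between these or near the lower figures. Even an ICC of 0.01 doubles the nominal error in the upper case.

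Two further inferences are tempting and not supported. The working does not show that 525 is wrong, since it was never a power figure. Nor does it show that between-school variance can never be obtained: the article plans no ICC, but the school data would allow one, imprecisely.

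**What to change.** - Replace the between-group t and chi-squared tests and the ordinary regressions with linear or logistic mixed models. Include a random intercept for school, a further one for class where whole classes were allocated, and site as a fixed effect.
- Use a small-sample correction such as Satterthwaite. Expect about 7 degrees of freedom if allocation is by school with four sites.
- Take the confidence interval for Cohen d from the same model.
- As a check, analyse arm-within-school (or class) means, using within-school differences where a school holds both arms. A plain t-test on school means is undefined for such schools.
- State how many schools hold both arms.
- As a secondary step, report the ICC with its 95% interval for each outcome and plan the future cluster trial on the upper part of that interval, because 12 schools estimate it only loosely.

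The cost is analysis wording, since school and class membership are known from recruitment. The price is wider intervals and few degrees of freedom. The model corrects the standard errors only; it does not remove confounding from non-random allocation or from volunteer selection.
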